## Abstract

**Background:**

Sepsis is a common cause for admission to the intensive care unit (ICU), and its incidence has been increasing. It is associated with a significant increase in serum inflammatory biomarkers such as C-reactive protein (CRP) and cytokines such as interleukin 1 (IL-1), IL-6, and tumor necrosis factor (TNF). Sepsis is also associated with pathophysiological changes that include fluid accumulation in the lungs, eventually leading to acute respiratory distress syndrome (ARDS), tissue edema, hypotension, and acute kidney injury (AKI). Conventional therapies include antibiotics, but these may have important adverse effects, so novel therapeutic approaches are required. In animal studies, l-carnitine improves antioxidant status, and in some clinical trials, it has been shown to reduce inflammation. It has also been shown to improve respiratory distress and help maintain coenzyme A homeostasis, metabolic flexibility, promoting the normal function of the tricarboxylic acid (TCA) cycle, and oxidation of fatty acids by peroxisomes. We aim to determine the effects of very high doses of l-carnitine on inflammatory factors, oxidative stress, and clinical outcomes of patients with sepsis in ICU.

**Method and design:**

In this double-blind, randomized controlled clinical trial, we will use block randomization of 60 patients with sepsis, aged between 20 and 65 years from Al-Zahra Hospital, Isfahan, Iran. The intervention group (*n* = 30) will receive three capsules of l-carnitine (each capsule contains 1000 mg l-carnitine; totally 3000 mg/day) for 7 days, and a control group (*n* = 30) will receive a placebo with the same dose and for the same duration in addition to usual care. At baseline, scores for clinical and nutritional status (Acute Physiology and Chronic Health Evaluation II (APACHE II), Sequential Organ Failure Assessment (SOFA), Quick SOFA (qSOFA), and NUTRIC Score) will be assessed. At beginning and end point of the study, inflammatory markers (CRP, erythrocyte sedimentation rate (ESR)), oxidative stress status (total oxidative stress (TOS), total antioxidant capacity (TAC)), and clinical variables will be evaluated also. The mortality rate will be assessed within 28 days of the beginning of the intervention.

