### Eligibility criteria {10}

Inclusion criteria:Septic patients who will be hospitalized in the ICU. Sepsis will be diagnosed using new definitions for sepsis and septic shock (Sepsis-3) by Surviving Sepsis Campaign International Guidelines for Management of Sepsis and Septic Shock: 2016 [17]. Septic patients will be recruited < 24 h after diagnosisAge between 20 and 65 yearsLegal guardian writes informed consentExclusion criteria:Patients who stay in hospital for < 3 daysPatients who receive parenteral nutritional supportPatients who receive enteral or oral nutrition at first but then transfer to parenteral nutrition due to the contraindicationsPatients who will not be able to receive enteral nutrition or those who will not be able to receive enteral nutrition in the future because of incomplete resuscitation and hemodynamic instability or gastrointestinal disorders including nausea, persistent vomiting, ileus, intestinal obstruction, uncontrolled diarrhea (> 500 ml/day), high-output fistula (> 500 ml/day), and intestinal inaccessibilityPatients with cancer undergoing chemotherapy and use cisplatin and other drugs that have interaction with l-carnitine; phenobarbital and phenytoin, pivalic acid, valproic acid and ifosfamide, and levetiracetamPatients undergoing dialysis, severe and progressive septic shock or sepsis, infection processes, DIC (diffuse intravascular coagulation), and any inflammatory interactions that interfere with the intervention process will be excludedPregnancyPatients with BMI < 18.5 kg/m^2^Patients who require frequent blood transfusionsAny unwanted side effects in patients after taking a supplement or placebo

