#### Intervention description {11a}

In both groups, after hemodynamic resuscitation and stabilization, nutritional support will begin in the first 24–48 h. Nutritional support with 25 kcal/kg of energy will be determined and will be administered as a bolus method, 7 times in 24 h. Patients will receive all common medications and routine treatment and will be visited daily by a physician who will assess gastrointestinal function.

The intervention will be as capsules in the form of 1000 mg of l-carnitine that will be manufactured by Karen Pharma and Food Supplement company, Iran. Placebo capsules of identical color, odor, and taste will also be produced by above mentioned company.

We consider 3000 mg as the appropriate intervention dose because this dose has low adverse effects and studies show that supplementation > 2 gr/day might have a greater effect [18–20]. l-carnitine and placebo will be tagged A and B by Karen Pharma and Food supplement company and prescribed to the patients using a double-blind procedure. Placebo or l-carnitine will be administered orally or with enteral nutrition (enteral tube feeding) three times a day in 9:00, 15:00, and 21:00 o'clock for 7 days (patients will receive totally 3000 mg l-carnitine or placebo for 7 days).

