#### Outcomes {12}

All assessors in this trial will be blinded to intervention allocation.

Serum CRP and ESR as an inflammatory agent, serum lactate dehydrogenase (LDH) as a marker of cell injury, total oxidative stress (TOS), and total antioxidant capacity (TAC) as an oxidative stress biomarker will be measured as our primary outcomes. Secondary outcomes include evaluating duration of hospitalization (days) and 28-day mortality rate, differences in albumin (Alb), alanine aminotransferase (ALT), aspartate aminotransferase (AST), blood urea nitrogen (BUN), and creatinine in blood. Anthropometric variables such as weight, height, body mass index (BMI), mid arm circumference (MAC), and calf circumference will be appraised at baseline.

Estimation of patient height: Due to the limitations in the ICU, the patients’ height is calculated based on the following formula [22]:
$$ \mathrm{Height}\ \left(\mathrm{cm}\right)=153.492-\left(7.97\times \mathrm{sex}\ \left[\mathrm{sex}:\mathrm{man}=1,\mathrm{woman}=2\right]\right)+\left(0.974\times \mathrm{ulna}\ \mathrm{length}\ \left[\mathrm{in}\ \mathrm{cm}\right]\right) $$

Estimation of patient weight: Due to the limitations in the ICU, the patients’ weight is calculated based on Chumlea I formula [23]:
$$ \mathrm{Men}:\left(\mathrm{MAC}\times 2.31\right)+\left(\mathrm{calf}\ \mathrm{circumference}\times 1.50\right)-50.10 $$$$ \mathrm{Women}:\left(\mathrm{MAC}\times 1.63\right)+\left(\mathrm{calf}\ \mathrm{circumference}\times 1.43\right)-37.46 $$

Blood drawing will be executed at baseline and end of the trial. About 10 ml volume of fasted blood (at 6:00 o’clock before first meal) will be collected and then centrifuged, with the serum separated from the sediment, and preserved at temperature of − 20 °C.

Calf circumference method of measurement: The circumference of the leg muscle is measured so that the patient is in the supine position. The patient’s left knee rises high enough to form a right corner between the thigh and the leg. We place the tape around the leg muscle and move it along the leg muscle to meter the largest circumference without any pressure to the subcutaneous tissue [24].

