#### Methods in analysis to handle protocol non-adherence and any statistical methods to handle missing data {20c}

Intention-to-treat analysis will be carried out for missing data. Patient exclusion reasons will be reported completely. We plan to perform sensitivity analyses to explore the effect of departures from the missing data assumptions made in the efficacy analyses. Multiple imputation will be used for missing data.

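### The 28-day mortality clock starts at treatment, not at randomisation, and the post-allocation exclusions can remove undosed patients despite the intention-to-treat statement

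*Protocol article*

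**What the plan says.** All places are in the protocol article.

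- **Time origin.** The abstract (Method and design) states: "The mortality rate will be assessed within 28 days of the beginning of the intervention". Outcomes {12} lists the endpoint without an origin: "Secondary outcomes include evaluating duration of hospitalization (days) and 28-day mortality rate".
- **Recruitment and allocation.** Eligibility criteria {10} says "Septic patients will be recruited" less than 24 h after diagnosis. Sequence generation {16a} speaks of recruiting patients straight into one arm or the other by means of a randomisation website. Implementation {16c} gives enrolment and assignment to the same investigator. No section says at what moment the envelope is opened.
- **Start of feeding and capsules.** Intervention description {11a} says that in both groups "after hemodynamic resuscitation and stabilization, nutritional support will begin in the first 24–48 h". On the capsules it says: "Placebo or l-carnitine will be administered orally or with enteral nutrition (enteral tube feeding) three times a day". It gives no first-dose time relative to diagnosis, randomisation or feeding.
- **Exclusions that can act after allocation.** Eligibility criteria {10} excludes hospital stays under 3 days, patients who switch to parenteral nutrition, and "those who will not be able to receive enteral nutrition in the future because of incomplete resuscitation and hemodynamic instability". Strategies to improve adherence {11c} excludes, at the end of the study, anyone who took under 80% of the capsules.
- **Analysis set.** Section {20c} says: "Intention-to-treat analysis will be carried out for missing data".

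**The concern.** A time-to-death or 28-day endpoint in a randomised trial should be counted from randomisation, so that every allocated patient has a defined follow-up window. Here the clock starts at an event, the first capsule, that some allocated patients may never reach. For them the mortality endpoint is undefined as written, and several exclusion rules offer a way to remove them altogether.

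Early deaths carry much of the information on mortality in sepsis. In a trial of 60, losing even a few of them changes the estimate and narrows the population it describes. Mortality is a secondary outcome, but Objectives {7} names it among the aims and the abstract's discussion points to a mortality benefit. If the mortality comparison silently becomes one of treated or adherent patients, the intention-to-treat label would not describe it.

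**Working it through.** **The plan's own figure.** The plan gives no calculation for mortality. Its sample size is for CRP and reproduces: n = 2 × (1.96 + 0.84)² × 37² / 30² = 23.85, so 24 per arm. Thirty per arm corresponds to 20% loss (24 / 0.80 = 30). This does not depend on the mortality clock.

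**Step 1: can allocation precede the first dose?** Recruitment comes less than 24 h after diagnosis, and {16a} links recruitment to an arm. Feeding begins in the first 24–48 h, after stabilisation. A tube-fed patient who gets capsules with the feed may therefore be allocated before the first capsule. Nothing holds allocation back until dosing, but nothing requires it to come earlier.

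**Step 2: what happens to a patient allocated but never dosed?**

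| Rule | Effect on this patient |
|---|---|
| Abstract: 28 days from start of treatment | No time zero |
| Outcomes {12}: 28-day mortality, no origin | Does not resolve it |
| {10}: stay under 3 days | Can remove an early death |
| {10}: cannot be enterally fed | Can remove a patient who stays unstable |
| {11c}: under 80% of capsules | Removes: 0 of 21 capsules (3 a day × 7 days) is 0% |
| {20c}: intention to treat | Should keep the patient |

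The last row cannot hold together with the three exclusion rows if those rules apply after allocation. The short-stay and 80% rules can only be judged after the event.

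**Step 3: how many patients could this be?** The documents give neither the length of the gap nor the timing of deaths, so this is illustration only. Assumptions: the 28.3% to 41% severe-sepsis mortality in Background and rationale {6a} applies over 28 days, and all 60 patients have the same gap of t days.

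F(t) = 1 − exp[−H × (t/28)^k], with H = −ln(1 − m). For m = 0.283, H = 0.333. For m = 0.41, H = 0.528.

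| Gap and hazard | m = 28.3% | m = 41% |
|---|---|---|
| t = 0 (allocation at first dose) | 0 of 60 | 0 of 60 |
| t = 2, constant hazard (k = 1) | F = 2.3%; 1.4 of 60 | F = 3.7%; 2.2 of 60 |
| t = 2, front-loaded (k = 0.5) | F = 8.5%; 5.1 of 60 | F = 13.2%; 7.9 of 60 |

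As a share of 28-day deaths, F/m is 8% to 9% with constant hazard and 30% to 32% with k = 0.5. The shape 0.5 is an assumption with no source in the documents.

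**Step 4: effect on the counted rate if those deaths were dropped.** The counted rate is (m − F)/(1 − F). With constant hazard and a 2-day gap, 28.3% becomes (0.283 − 0.0235)/(1 − 0.0235) = 26.6%, and 41% becomes (0.41 − 0.037)/(1 − 0.037) = 38.7%.

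**The case against.** The strongest reply is that the gap may not exist. The 24–48 h window is attached to feeding, its starting point is not stated, and capsules may also be taken orally. One investigator enrols, assigns from the envelope and gives the capsules, so the envelope may well be opened at first dose. In that case nobody is lost this way. This stands as a possibility, but the protocol does not say so.

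Three stronger readings are tempting, and the documents do not support them.

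- A reader might infer that capsules always wait for feeding at 24–48 h. The text supports only that they may start later than allocation.
- A reader might infer that deaths before dosing go uncounted because of the clock. No section says this. The abstract sentence sets a follow-up horizon, not a denominator, and {20c} states intention to treat. Actual removal would come from the exclusions in {10} and {11c}.
- A reader might infer bias between arms. Under blinded placebo, an event before the first capsule cannot be caused by the assigned capsule, so pre-dose losses should be similar in both arms.

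It is also fair that the mortality range in Step 3 fits imperfectly. It refers to severe sepsis, whereas the trial excludes severe and progressive cases and patients over 65, and it gives every patient the full 2-day gap.

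What remains is that the origin is stated once, is not tied to randomisation, and sits beside exclusions that contradict the declared analysis set.

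**Conclusion.** The point holds in this limited form: mortality has no time zero for a patient allocated but not dosed, and the short-stay, feeding and 80% rules can remove that patient in conflict with intention to treat. The number affected is unknown. It is zero if allocation takes place at first dose. It is about 1 to 2 of 60 for a full 2-day gap with constant hazard, and about 5 to 8 of 60 only if a front-loaded hazard is assumed. These figures rest on the assumptions in Step 3.

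The cost is fewer events, a narrower population and an analysis set that does not match its label. The expectation of similar loss in both arms covers pre-dose events only; what the exclusions remove after dosing has begun is not sized here. The point is worth correcting before recruitment, though it concerns a secondary outcome and does not touch the CRP sample size.

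**What to change.** 1. Keep screening and consent within 24 h of diagnosis, but state in the allocation sections ({16a} to {16c}) that the envelope is opened only when the first capsule is about to be given.
2. In the abstract and in Outcomes {12}, define mortality as death within 28 days of randomisation, for every randomised patient, whether or not any capsule was taken.
3. Reconcile {10} and {11c} with {20c}: the stay, feeding and adherence exclusions must not remove randomised patients from the mortality analysis. A per-protocol set that applies them can be kept as a sensitivity analysis. Without this step the first two changes do not deliver a count of all randomised patients.

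The cost is a few sentences and one change in the order of enrolment steps. Some consented patients will never be randomised and must be listed as screened only, so deaths between consent and first dose stay outside the comparison, but openly so. Feeding, dose and capsule timing are unchanged.

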**Discussion:**

Because of the anti-inflammatory and antioxidant properties of l-carnitine, it is possible that using a high dose of 3000 mg daily of this nutritional supplement may reduce inflammation and oxidative stress and improve subsequent mortality of critically ill patients with sepsis.

**Trial registration:**

Iranian Registry of Clinical Trials IRCT20201129049534N1. Registered on 2 May 2021.

## Administrative information

Note: the numbers in curly brackets in this protocol refer to the SPIRIT checklist item numbers. The order of the items has been modified to group similar items (see https://www.equator-network.org/reporting-guidelines/spirit-2013-statement-defining-standard-protocol-items-for-clinical-trials/).

## Introduction

### Background and rationale {6a}

Sepsis is often associated with an immunological reaction. It can result in organ malfunction and eventually death [1]. The immune system recognizes pattern recognition receptors of infective pathogens (PARPs), and the stimulation of the immune system leads to the secretion of pro-inflammatory cytokines such as interleukin 1 (IL-1) and tumor necrosis factor-α (TNF-α) and anti-inflammatory biomarkers. The normal response to infection results in a balance between these inflammatory molecules. In severe sepsis, this equilibrium is put out of kilter and may cause “life-threatening organ dysfunction” [2].

The incidence of sepsis has recently increased globally and is the leading cause of death on, and admission to, intensive care units (ICUs) [3]. More than 30 million people are affected by sepsis worldwide yearly, and this leads to 6 million deaths. The incidence of septic shock and severe sepsis in the USA is approximately 300/100,000 per year and cost more than $20 million in 2011 [4]. The mortality rates in severe sepsis were almost 41% in Europe against around 28.3% in the USA (The Surviving Sepsis Campaign 2012) [1].

Several adverse outcomes are attributed to the sepsis, including endothelial damage (arising from abnormal homeostasis and leading to fluid leak), edema of tissue, hypotension, vascular vasodilatation, and diminished tissue perfusion. Fluid accumulation in the lung can adversely affect gas exchange and lead to acute respiratory distress syndrome (ARDS). Acute kidney injury (AKI) can result from direct effects of cytokines, injury to the microvasculature or tissue perfusion reduction, and a dysregulated coagulation system [2]. Pro-inflammatory cytokines and inflammatory biomarkers, such as C-reactive protein (CRP), IL-1, IL-6 and TNF-α, increase after the development of sepsis [5–7]. Most common therapeutics strategies for controlling this condition are antimicrobials therapies such as antibiotics, antifungals, and antivirals, fluid therapy, vasopressor therapy, ventilation support, activated protein C, and other adjunctive therapies such as corticosteroids, vitamin C, and vitamin B1 [8, 9].

The principal problem is a lack of a specific pharmacological therapy for pathophysiology of sepsis, while many investigations carried out over the last 50 years [10]. Thus, there is a need for the development of new treatments, or new adjunctive treatments. The major metabolic consequences of sepsis include hyperglycemia, ketosis, increased plasma free fatty acids (FFAs), and hyperlactatemia. Specifically, hyperlactatemia indicates tissue hypoperfusion and anaerobic metabolism [10].

l-carnitine is a safe and well tolerated food supplement [11]. l-carnitine enhances FFAs transport into the mitochondria, removing their pernicious effects from the cytoplasm, and separating acetate in mitochondria. Thus, it may alleviate some metabolic malfunction in septic patients [10]. In addition, l-carnitine enhanced superoxide dismutase 2 (SOD2) expression and was anti-inflammation and reduced oxidative stress when studied in animal studies. It reduced several inflammatory mediators like nuclear factor kappa B (NF-ĸB), IL-1, and IL-6, and reduced inflammation of organs. In previous clinical trials which were conducted on hemodialysis patients, on septic shock patients, on coronary artery disease patients, and on perioperative atrial fibrillation patients, it has been shown that this nutrient significantly decreased CRP and the mortality rate [11]. l-carnitine at doses > 2 g per day is more effective in reducing inflammation and in improving health status. Reducing oxidation of lipids, enhancing anti-oxidative stress defense system, and metal ion chelating lead to combat oxidative stress by this nutrient [12]. In a previous trial, l-carnitine supplementation among patients admitted to the neonatal intensive care unit (NICU) with respiratory distress syndrome (RDS) resulted in increasing serum carnitine level. In comparison to control group, the ventilator use period and need for surfactant therapy was also reduced [13]. Some other anti-inflammatory agents that may also be used in sepsis include ulinastatin, which is a serine protease inhibitor that can reduce IL-6, IL-8, TNF-α, and CRP and can alleviate injury of mitochondria and has anti-oxidant effects; thymosin α-1 (Tα1), which is a thymic peptide regulates immune system and so can decrease mortality rate in septic patients [14]; and anisodamine, another medicinal treatment choice for septic shock. It improves blood circulation and reduces TNFα in these patients [15]; besides, anisodamine can combat oxidative agents, act as anti-oxidant, and prevent mitochondrial damage [16].

### Objectives {7}

We aim to investigate the effects of high dose l-carnitine supplementation on inflammatory mediators, oxidative stress, clinical outcomes, and the rate of mortality in ICU septic patients. If this trial confirms our hypothesis, supplementation with l-carnitine may be used to improve the effects of existing therapies.

### Study design {8}

A randomized, parallel, two-arm, double-blind and placebo-controlled superiority clinical trial will be implemented.

## Methods: participants, interventions, and outcomes

### Setting {9}

Our study will be performed in Al-Zahra hospital, an academic hospital, affiliated to Isfahan University of Medical Sciences, Isfahan, Iran.

### Eligibility criteria {10}

Inclusion criteria:Septic patients who will be hospitalized in the ICU. Sepsis will be diagnosed using new definitions for sepsis and septic shock (Sepsis-3) by Surviving Sepsis Campaign International Guidelines for Management of Sepsis and Septic Shock: 2016 [17]. Septic patients will be recruited < 24 h after diagnosisAge between 20 and 65 yearsLegal guardian writes informed consentExclusion criteria:Patients who stay in hospital for < 3 daysPatients who receive parenteral nutritional supportPatients who receive enteral or oral nutrition at first but then transfer to parenteral nutrition due to the contraindicationsPatients who will not be able to receive enteral nutrition or those who will not be able to receive enteral nutrition in the future because of incomplete resuscitation and hemodynamic instability or gastrointestinal disorders including nausea, persistent vomiting, ileus, intestinal obstruction, uncontrolled diarrhea (> 500 ml/day), high-output fistula (> 500 ml/day), and intestinal inaccessibilityPatients with cancer undergoing chemotherapy and use cisplatin and other drugs that have interaction with l-carnitine; phenobarbital and phenytoin, pivalic acid, valproic acid and ifosfamide, and levetiracetamPatients undergoing dialysis, severe and progressive septic shock or sepsis, infection processes, DIC (diffuse intravascular coagulation), and any inflammatory interactions that interfere with the intervention process will be excludedPregnancyPatients with BMI < 18.5 kg/m^2^Patients who require frequent blood transfusionsAny unwanted side effects in patients after taking a supplement or placebo

